## Abstract

**Background:**

BRCA1/2 mutation carriers are recommended to undergo risk-reducing salpingo-oophorectomy (RRSO) at 35 to 45 years of age. RRSO substantially decreases ovarian cancer risk, but at the cost of immediate menopause. Knowledge about the potential adverse effects of premenopausal RRSO, such as increased risk of cardiovascular disease, osteoporosis, cognitive dysfunction, and reduced health-related quality of life (HRQoL), is limited.

**Objective:**

The aim of this study is to assess the long-term health effects of premenopausal RRSO on cardiovascular disease, bone health, cognitive functioning, urological complaints, sexual functioning, and HRQoL in women with high familial risk of breast or ovarian cancer.

**Methods:**

We will conduct a multicenter cross-sectional study with prospective follow-up, nested in a nationwide cohort of women at high familial risk of breast or ovarian cancer. A total of 500 women who have undergone RRSO before 45 years of age, with a follow-up period of at least 10 years, will be compared with 250 women (frequency matched on current age) who have not undergone RRSO or who have undergone RRSO at over 55 years of age. Participants will complete an online questionnaire on lifestyle, medical history, cardiovascular risk factors, osteoporosis, cognitive function, urological complaints, and HRQoL. A full cardiovascular assessment and assessment of bone mineral density will be performed. Blood samples will be obtained for marker analysis. Cognitive functioning will be assessed objectively with an online neuropsychological test battery.

**Results:**

This study was approved by the institutional review board in July 2018. In February 2019, we included our first participant. As of November 2020, we had enrolled 364 participants in our study.

**Conclusions:**

Knowledge from this study will contribute to counseling women with a high familial risk of breast/ovarian cancer about the long-term health effects of premenopausal RRSO. The results can also be used to offer health recommendations after RRSO.

**Trial Registration:**

ClinicalTrials.gov NCT03835793; https://clinicaltrials.gov/ct2/show/NCT03835793.

**International Registered Report Identifier (IRRID):**

DERR1-10.2196/24414

## Introduction

### Background

Female *BRCA1* germline mutation carriers have a cumulative risk of 44% to develop ovarian cancer before the age of 80 years. For *BRCA2* mutation carriers, this cumulative risk is 17% [1]. In the absence of an effective screening method for ovarian cancer, risk-reducing salpingo-oophorectomy (RRSO) is advised at an age when there is a high risk of developing ovarian cancer (before the age of 35-40 years for *BRCA1* mutation carriers and at the age of 40-45 years for *BRCA2* mutation carriers) provided that the woman no longer has a wish to have children [2,3]. During this procedure, both ovaries and fallopian tubes are removed. Since 2009, the uptake of RRSO in *BRCA1/2* mutation carriers in the Netherlands has increased greatly from 81% to 98% currently [4-6]. While RRSO at the recommended age decreases the risk of ovarian cancer by around 96% [7,8], it also initiates premature surgical menopause owing to a sudden drop in the levels of ovarian hormones. Whether RRSO also reduces the risk of breast cancer is currently debated. Various early studies have reported a risk reduction of 50%, but this is a substantial overestimation owing to bias [8-11].

The relationship between early menopause (either surgically induced or due to premature ovarian insufficiency [POI]) and noncancer health outcomes, including cardiovascular disease (CVD), osteoporosis, cognition, and health-related quality of life (HRQoL), has been examined previously. However, most of the published studies had a limited follow-up (median <5 years), which is too short to establish an association with long-term health effects [12-15]. Additionally, hormone replacement therapy (HRT) use, cancer treatment, and lifestyle may alter the potential association of RRSO with noncancer health outcomes. *BRCA1/2* mutation carriers may have been treated for breast cancer, which can be cardiotoxic and potentially have a negative impact on the brain [16-19]. Lastly, women with a high familial risk of breast/ovarian cancer may have a healthier lifestyle than age-matched women without a family history of breast cancer, rendering translation of results of previous research on early menopause to this specific population difficult [20].

### Early Menopause and Cardiovascular Risk

Before the age of 50 years, female sex hormones, such as estrogen and progesterone, are likely to protect women against CVD as they have atheroprotective properties [21,22]. Previous studies have shown that women with POI are at higher risk of developing CVD and that earlier age at menopause is associated with a higher cardiovascular mortality rate [23-26]. Additionally, a higher risk of CVD has been observed after *surgical* menopause compared with *natural* menopause [27]. However, age at surgical menopause was often not specified or surgery was performed at later ages than the recommended young ages for RRSO in *BRCA1/2* mutation carriers. Thus, information about the cardiovascular risk of *early* surgical menopause is still limited [27-29]. Furthermore, it is possible that early loss of ovarian hormones is not the *cause* of the higher cardiovascular disease risk in women with POI. The reverse causality hypothesis postulates that POI is the result of accelerated vascular aging, which would also explain a statistical (noncausal) association between earlier natural menopause and increased CVD risk [30]. If this is true, no elevated CVD risk would be expected in women with early surgical menopause due to RRSO.

### Early Menopause and Bone Health

Reproductive hormones play a role in maintaining bone health. Estrogen suppresses bone resorption and stimulates bone formation [31]. Postmenopausal women aged 50 to 55 years have a higher incidence of hip fractures than age-matched premenopausal women, and among postmenopausal women, the incidence of hip fractures rises with age [32]. However, data on the long-term effect of early (surgical or natural) menopause on bone health are limited owing to short follow-up periods.

### Early Menopause and Cognition

The neuroprotective effects of estrogens, progestogens, and androgens have been described in several studies [33]. Rocca et al observed that women who underwent premenopausal oophorectomy (before 56 years of age) for benign reasons had a higher risk of cognitive impairment than age-matched women without oophorectomy [34]. There was a trend for more severe cognitive impairment with younger age at oophorectomy for both unilateral and bilateral oophorectomies. However, information on *BRCA1/2* mutation carriership was not provided [34]. Additionally, Bove et al observed a faster decline in global cognition in women with an earlier age at surgical menopause [14]. Thus, while there are some data on the effect of surgical menopause on cognition, research on *BRCA1/2* mutation carriers is limited.

### Early Menopause and HRQoL

RRSO may have an important impact on HRQoL, including generic issues, such as physical, role, and emotional functioning, as well as cancer-related anxiety, sexual functioning, and menopause-specific symptoms [12,35,36]. However, it is not known whether these effects persist over time. A recent study with a mean follow-up of 7.9 years after RRSO found that moderate to severe menopausal complaints were still present in almost 70% of women who underwent premenopausal RRSO, without any improvement over time [37]. The magnitude of the effect of RRSO on sexual functioning and endocrine symptoms is modulated by HRT use [38,39]. However, HRT use is contraindicated for *BRCA1/2* mutation carriers with a history of breast cancer.

The number of postmenopausal years is associated with an increased prevalence of vulvovaginal atrophy [40]. Atrophy of the urethral epithelium may lead to urinary incontinence. To our knowledge, no research has been conducted on the association between early surgical menopause and urinary incontinence, although this generally has a severe impact on sexual functioniƒng and quality of life [41,42].

Figure 1 provides a schematic overview of the effects of a decrease in estrogen levels due to menopause on various organ systems.

**Figure 1 figure1:**
[figure not shown]
Overview of the effects of reduced estrogen levels on various organ systems.

A recent Cochrane systematic review on the benefits and harms of RRSO in women with a *BRCA1/2* mutation stated that no conclusions can be drawn regarding bone fracture incidence and HRQoL, and that further research is needed. CVD and cognition were not included as outcomes in this review, probably because of the paucity of studies [43]. Therefore, the aim of the HARMOny study (Health After eaRly Menopause due to Oophorectomy) is to investigate the long-term health effects of RRSO. We will conduct a cross-sectional study with prospective follow-up nested in a large Dutch cohort. We hypothesize that women with surgically induced premature menopause are at higher risk of subclinical CVD, compromised bone health and osteoporosis, reduced HRQoL, and impaired cognitive functioning, compared to age-matched women with natural menopause after the age of 50 years. Depending on the results, this may lead to active surveillance of the above health problems to improve long-term health and HRQoL in women who have undergone early RRSO.

## Methods

### Study Aim

The primary aim of our study is to assess the long-term health effects of RRSO on subclinical CVD, bone mineral density (BMD), and cognitive functioning in women at increased familial risk of breast or ovarian cancer mainly due to a *BRCA1/2* mutation. Our secondary study aims are to assess overall HRQoL, endocrine symptoms, such as hot flashes and night sweats, sexual functioning, urogenital problems, and the prevalence of cardiovascular risk factors.

### Recruitment

We will include 500 women who have undergone RRSO before the age of 45 years, with a follow-up period of at least 10 years (the early RRSO group). We will compare them with 250 women from the same cohort (frequency matched on current age) who have not undergone preventive RRSO or have undergone RRSO at the age of 55 years or above (the late/non-RRSO group). The exclusion criteria are a metastatic disease; a serious physical comorbidity or psychiatric disorder; a language barrier; a metal cardiac valve; a bare metal coronary stent, since the reflection of the stent would interfere with the computed tomography scan; and natural POI before the age of 40 years. A history of nonovarian cancer, including breast cancer, is not a reason to be excluded.

Eligible women who are alive will be invited for a clinic visit and questionnaire survey that will assess CVD status, BMD, cognitive functioning, and HRQoL. For eligible women who have died, we will collect information on the causes of death to examine selection bias.

Participants will be selected from the dynamic nationwide HEBON study cohort, a national collaboration on HEreditary Breast and Ovarian cancer in the Netherlands, with women tested for *BRCA1/2* germline mutations included since 1997 by all eight Dutch University Medical Centers (UMCs) and the Netherlands Cancer Institute (NKI). The cohort currently consists of over 3600 proven female *BRCA1/*2 germline mutation carriers. Participants have given informed consent for linkage with the Netherlands Cancer Registry and the Dutch Nationwide Pathology Database (PALGA), which can provide information on all prophylactic mastectomies and salpingo-oophorectomies performed in the Netherlands since 1991. This provides us with nearly complete information on the occurrence of RRSO. Data on lifestyle, family history, reproductive factors, and hormone use have been collected from HEBON participants through questionnaires [44].

Figure 2 provides a schematic overview of the patient selection and eligibility criteria of our study population.

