### Statistical Analysis

We will analyze differences in the cardiovascular risk profile, BMD, and neurocognitive functioning between the early RRSO group and the late/non-RRSO group using multivariable linear regression analyses and logistic regression analyses with clinically relevant cutoff points for the outcomes of interest. The analyses will be adjusted for confounders, including lifestyle, reproductive factors, and medication use, where applicable. For the analysis of patient-reported outcomes, such as HRQoL, sexual functioning, and menopausal symptoms, we will use mixed effect models.

We expect approximately 40% of the women to have a breast cancer history and will perform the analyses separately in women with and those without a breast cancer history, as breast cancer treatment may affect outcomes. Additional subgroup analyses will be performed according to HRT use (yes/no), *BRCA1/2* mutation status, age at RRSO (<40 years/≥40 years), and time since RRSO (10-15 years/>15 years).

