One of the major strengths of our study is that it will be the first to examine the health effects of premenopausal RRSO at less than 45 years with a follow-up of over 10 years compared to controls with natural menopause. Additionally, owing to the large number of participants, we will have sufficient power for subgroup analyses. A limitation of our study could be survivor bias. Owing to the inclusion criterion of at least 10 years of follow-up, patients may already have died of relevant study outcomes before study inclusion. However, as we conduct the cross-sectional study within a well-characterized cohort, we can assess the extent of such bias by collecting cause of death information for potentially eligible but already deceased women.

This initial cross-sectional study will provide prevalence rates of noncancer outcomes. Therefore, we will follow the study cohort prospectively to obtain incidence rates of outcomes of interest and evaluate changes in outcomes over time.

To summarize, the current literature lacks information on long-term noncancer outcomes in women at increased risk of breast/ovarian cancer who have undergone early oophorectomy. With this study, we will be able to provide insights into the prevalence and severity of CVD, osteoporosis, cognitive impairment, and HRQoL effects after RRSO. This knowledge will yield evidence-based information for women and for health care providers about the long-term effects of early RRSO. The results can be incorporated in decision-support tools about risk-reducing surgeries in *BRCA1/2* mutation carriers considering RRSO and can be used to offer individualized counseling about additional screening and interventions for noncancer diseases or complaints after RRSO.

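### The stated contrast is with natural menopause after age 50, but the written criteria define comparators by RRSO status only, so women with earlier loss of ovarian function are admitted and may dilute that contrast

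*Protocol article*

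**What the plan says.** The protocol article describes the comparison group in three places.

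- **Introduction, last paragraph (hypothesis).** Women with surgically induced premature menopause are expected to do worse "compared to age-matched women with natural menopause after the age of 50 years".
- **Methods, Recruitment.** The comparators are women "who have not undergone preventive RRSO or have undergone RRSO at the age of 55 years or above (the late/non-RRSO group". The one exclusion that concerns menopause is "and natural POI before the age of 40 years". Cancer survivors are eligible: "A history of nonovarian cancer, including breast cancer, is not a reason to be excluded".
- **Discussion, strengths.** The study is presented as examining premenopausal RRSO "with a follow-up of over 10 years compared to controls with natural menopause".

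Under Statistical Analysis, the plan adds: "We expect approximately 40% of the women to have a breast cancer history and will perform the analyses separately". The further subgroups are HRT use, mutation status, age at RRSO and time since RRSO. Reproductive factors and medication use appear as adjustment variables. No stratum or subgroup uses the comparator's age at, or cause of, loss of ovarian function.

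For the early group, the Objective names premenopausal RRSO as the exposure. The text of Recruitment asks only for surgery before 45 and at least 10 years of follow-up.

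**The concern.** The hypothesis and the Discussion define the control condition by the timing and nature of menopause. The criteria define it by whether and when preventive surgery took place. These are different populations. Under the written criteria a comparator may have had natural menopause at 43, ovarian failure after chemotherapy at 41, or an oophorectomy for a benign indication. None of these women had natural menopause after 50, and each had some of the oestrogen loss whose effect is being studied.

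If the study's own hypothesis is right, such women raise the comparator risk and pull the observed difference below the one named. The article intends the results for counselling and decision support. A small or null difference could then be read as reassurance about early surgical menopause as against menopause after 50, which is not what the unrestricted comparison estimates.

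A smaller matter of the same kind is that the criteria as written do not secure premenopausal status at surgery in the early group.

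**Working it through.** **1. Reproduce the plan's figures.** Inputs from Sample Size Calculation: 250 comparators, 500 early RRSO, CAC above 100 in 10% of comparators, odds ratio 1.9, α 5% (sidedness not stated; two-sided used).

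- Rate at OR 1.9: 0.10 × 1.9 / (0.90 + 0.10 × 1.9) = 0.19 / 1.09 = 17.4%.
- Power = Φ[(d − 1.96·SE0) / SE1], where SE0 = √[p̄(1−p̄)(1/250 + 1/500)] and SE1 = √[p0(1−p0)/250 + p1(1−p1)/500]. Result: 78.6%, against the stated 80%.
- Cognition, effect size 0.25: SE = √(1/250 + 1/500) = 0.0775; power = Φ(0.25/0.0775 − 1.96) = 89.8%, against the stated 90%.

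Both reproduce, so the point does not rest on an arithmetic error in the plan.

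**2. Dilution model (assumption).** Let c be the share of comparators with early loss of ovarian function and k the fraction of the early-RRSO effect they carry. The documents give neither. With the plan's hypothesised 20% v 10%, the comparator rate is 0.10 + c·k·0.10. Without dilution the odds ratio is 2.25 and power 95%.

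Worked case, c = 20%, k = 1:
- p0 = 0.12, p1 = 0.20, d = 0.08
- OR = (0.20/0.80) / (0.12/0.88) = 1.83
- p̄ = (30 + 100)/750 = 0.173, SE0 = 0.0293, SE1 = 0.0272
- power = Φ[(0.08 − 0.0575)/0.0272] = 80%

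The last column drops the affected comparators, leaving 250(1−c) against 500, at 10% v 20% (OR 2.25).

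| c | k = 1: OR, power | k = 0.5: OR, power | Restricted: comparators, power |
|---|---|---|---|
| 10% | 2.02, 89% | 2.13, 93% | 225, 94% |
| 20% | 1.83, 80% | 2.02, 89% | 200, 92% |
| 30% | 1.67, 67% | 1.92, 85% | 175, 88.5% |

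**3. Cognition and BMD, same model.**
- Cognition: at c = 20%, k = 1, the effect size becomes 0.25 × 0.8 = 0.20 and power 73%; 200 unaffected comparators at 0.25 give 85%. With k = 0.5 the effect size is 0.25 × 0.9 = 0.225 and power 83%.
- BMD (0.07 g/cm², SD 0.15): at c = 30%, k = 1, the difference becomes 0.07 × 0.7 = 0.049. The SE is 0.15 × 0.0775 = 0.0116, so power is 99%. It is still 95% at c = 40%. The estimate shrinks, but the power hardly changes.

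**4. Does the planned analysis already separate these women?** Analysing women with and without breast cancer separately takes menopause caused by breast cancer treatment out of the no-cancer stratum. It leaves it in the cancer stratum and does nothing about natural menopause at 40-50. Age at RRSO and time since RRSO describe only women who had the operation. Adjusting for reproductive factors would not restore the contrast either: age at menopause is close to the exposure itself.

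**The case against.** The strongest reply is that RRSO status is the right basis for the comparison. The primary aim is the long-term effect of RRSO, and the intended readers are women deciding whether to have it. Their alternative is keeping the ovaries, with whatever age at menopause follows, so natural menopause at 40-50 belongs to that alternative and is not contamination. Requiring comparators to have had ovarian function to 50 selects on a later event, and this cannot be mirrored in the early group, which includes women who would have had menopause at 40-50 anyway. The Introduction and Discussion also describe the hypothesis that vascular ageing causes early menopause. If that is so, removing such women from the comparators alone would leave a vascularly healthier control group and push cardiovascular results away from the null. This argument stands. It is why the restriction should not become the main analysis.

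Three stronger inferences are tempting and not supported.

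- **Every outcome is biased towards no effect, most of all among breast cancer survivors.** The Discussion cites a study in which treatment-induced POI did not affect cardiovascular risk. If that applies here, this component would not dilute the CAC contrast, though bone and cognition could still be affected.
- **The expected 40% with breast cancer approximates the affected share.** It counts any breast cancer history, including diagnoses after menopause.
- **The full-effect figures are the expected loss.** They treat menopause at 49 like oophorectomy at 38. With half the effect, restriction raises CAC power by only about 1 to 4 points.

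It can also be said that the eligibility schematic (Figure 2) is not available here and might add a criterion, and that sensitivity sets are ordinary SAP content. The first limits certainty about what is excluded, above all for premenopausal status in the early group. The second does not remove the conflict, because the hypothesis and the criteria are both written out in the article and disagree.

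**Conclusion.** The mismatch holds on the text and does not depend on any assumed share: the article names natural menopause after 50 as the control condition and recruits by RRSO status. The size of the consequence is uncertain. For CAC above 100, an assumed share of 10-30% takes the odds ratio from 2.25 to 2.02-1.67 (power 89-67%) with full effect, or to 2.13-1.92 (power 93-85%) with half effect. Cognition is affected to a similar degree; BMD power is not materially affected. These figures rest on the assumed c and k and on the plan's 20% v 10%.

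A reader might infer that the RRSO-status comparison is invalid or should be replaced. It is not invalid: it answers a relevant question, but a different one from the question stated. What cannot be claimed from it is a contrast with natural menopause after 50. The point is worth settling before analysis, since it changes what the study may conclude.

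**What to change.** 1. **Reconcile the wording.** In the hypothesis and the Discussion, state that the RRSO-status comparison estimates the effect of early RRSO against keeping the ovaries, whatever age at menopause follows. Say how comparators with a non-preventive oophorectomy are treated, since they did not keep theirs. Do not describe the unrestricted comparators as women with natural menopause after 50.
2. **Pre-specify one key supporting analysis for all primary outcomes** (subclinical CVD, BMD, cognition). Classify women by age and cause of loss of ovarian function; restrict comparators to those with ovarian function to at least age 50 and the early group to those premenopausal at RRSO. Present it beside the RRSO-status comparison, overall and within the breast cancer strata.
3. **Use data already being gathered:** the cohort's reproductive data, the study questionnaire and the breast cancer treatment records. Check that age at and cause of menopause can be derived for every comparator. With 136 of 250 comparators enrolled in November 2020, any missing item could still be added for the remaining 114.
4. **Report the share** of comparators with earlier loss of ovarian function, by cause, so that readers can judge the dilution.

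The cost is some protocol and SAP wording and perhaps a questionnaire item; no one need be removed from the study. The supporting analysis has fewer women (for example 200 comparators if the share is 20%) and conditions comparators on an event after the exposure decision. That selection should be stated as a limitation alongside its result.

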At present, it is still unclear whether early surgical menopause can be considered as a clinically relevant risk factor for CVD. During normal menopausal transition, CVD risk increases [23,26,78,80]. Women with an early natural menopause (<40 years) are at higher risk of developing CVD, and they have a higher CVD mortality than age-matched peers [23-26]. However, it has been debated whether this association is causal, and it has been speculated that this might also be explained by early vascular aging predisposing to both POI and cardiovascular disease [30,81]. If this is true, an artificial early menopause might not be associated with increased CVD risk. In support of this, a recent study by Krul et al showed that cancer treatment–induced POI did not affect CVD risk [82]. This renders it even more interesting to investigate CVD risk in women with surgically induced early menopause. To date, this has been addressed in only a few studies, with inconsistent results and with a median follow-up of at the most 5 years, which is too short considering potential delayed effects of estrogen deprivation and the long life expectancy of these women. Furthermore, previous studies vary with respect to HRT use and age at surgery [27-29].

The association between early surgical menopause and long-term bone health has also been rarely examined. Studies were inconclusive regarding decreased BMD and increased fracture risk, and whether these risks remain increased over time [83,84]. In addition, the effect of early RRSO on cognition has not yet been examined. However, both unilateral and bilateral oophorectomies at later ages have been associated with cognitive impairment and dementia, suggesting neuroprotective effects of estrogen on the brain. These effects appear to be age dependent [34,85].

After menopause, women more often report sexual and urogenital problems, such as urinary incontinence, recurrent urinary tract infections, impaired libido, and dyspareunia, which interfere with HRQoL. Women with POI experience these problems even more [86,87]. We do not know if these results can be generalized to surgical early menopause. Studies on long-term HRQoL after RRSO are limited and highly biased by HRT use.

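### The reference group is defined by RRSO status, yet the hypothesis and Discussion describe controls with natural menopause; women with early surgical or treatment-induced menopause can be counted as unexposed

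*Protocol article*

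**What the plan says.** Three places in the protocol article describe the controls.

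- The closing paragraph of the Introduction (after Figure 1) gives the hypothesis: women with surgically induced premature menopause are "compared to age-matched women with natural menopause after the age of 50 years".
- The Discussion, listing the study's strengths, says that early RRSO will be "compared to controls with natural menopause".
- Methods, Recruitment, sets the entry rule for the late/non-RRSO group: women "who have not undergone preventive RRSO or have undergone RRSO at the age of 55 years or above".

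The only exclusion in Recruitment that concerns menopause is "natural POI before the age of 40 years". On prior cancer it says: "A history of nonovarian cancer, including breast cancer, is not a reason to be excluded".

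Statistical Analysis adds: "We expect approximately 40% of the women to have a breast cancer history". It says the investigators "will perform the analyses separately in women with and those without a breast cancer history, as breast cancer treatment may affect outcomes". The adjustment set is lifestyle, reproductive factors and medication use; the further subgroups are HRT use, mutation status, age at RRSO and time since RRSO. Neither list names age at menopause or its cause.

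**The concern.** The entry rule and the two descriptive passages do not pick out the same women. Under the Recruitment wording, three kinds of women who do not fit the hypothesis can be controls:

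1. Women whose ovaries were both removed for a benign reason, at any age, because only preventive surgery is barred.
2. Women made menopausal by cancer treatment, because prior non-ovarian cancer is allowed and only natural ovarian insufficiency is excluded.
3. Women with natural menopause between 40 and 50.

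The first two kinds can have lost ovarian function early, which is the exposure being studied. The protocol's own background treats benign oophorectomy as an exposure of interest: the cognition study it cites compared women operated on for benign reasons with women not operated on, and the Discussion notes that "both unilateral and bilateral oophorectomies at later ages have been associated with cognitive impairment and dementia". That does not show that such women are in the reference group, only that counting them as unexposed would matter if they are.

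At stake are the direction of a possible bias in the primary comparisons and whether the conclusion, worded as a comparison with natural menopause, would describe the women analysed.

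**Working it through.** **Side by side**

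| Type of control | Hypothesis (natural, after 50) | Recruitment rule |
|---|---|---|
| Natural menopause after 50, no RRSO | in | in |
| Natural menopause at 40 to 50 | out | in |
| Treatment-induced menopause | out | in |
| Bilateral oophorectomy for a benign reason | out | in |
| Natural menopause before 40 | out | out |

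**Inputs from Sample Size Calculation.** 250 controls and 500 early-RRSO women; 10% of controls with a calcium score above 100; odds ratio 1.9 with 80% power at α 5% (taken as two-sided); hypothesised 20% in the early group; bone density difference 0.07 with SD 0.15; cognition effect size 0.25 with 90% power, two-tailed.

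**Assumption.** Let f be the share of controls who lost ovarian function early and carry the full early-RRSO risk. The document gives no value for f; 10% and 20% are illustrations.

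**Reproducing the stated power**

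- Calcium: p1 = 1.9 × 0.10 / (0.90 + 1.9 × 0.10) = 0.1743. Power = Φ[(p1 − p0 − 1.96·SE0)/SE1], with SE0 pooled = 0.0276 and SE1 unpooled = 0.0255. This gives Φ[(0.0743 − 0.0541)/0.0255] = 78.6%, against the stated 80%.
- Cognition: Φ[0.25 × √(250·500/750) − 1.96] = Φ[3.23 − 1.96] = 89.8%, against the stated 90%.
- Bone density: 0.07/0.15 = 0.467, and Φ[0.467 × 12.91 − 1.96] exceeds 99.9%.

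**Dilution.** The observed control rate is (1 − f) × 10% + f × p1. Mean differences are multiplied by (1 − f).

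| f | Calcium, true OR 1.9: control rate, observed OR, power | Calcium, 20% vs 10%: observed OR, power | Cognition: effect, power | Bone density: difference, power |
|---|---|---|---|---|
| 0 | 10.0%, 1.90, 78.6% | 2.25, 95.2% | 0.25, 89.8% | 0.070, >99.9% |
| 10% | 10.7%, 1.75, 68.3% | 2.02, 89.2% | 0.225, 82.8% | 0.063, >99.9% |
| 20% | 11.5%, 1.63, 56.9% | 1.83, 79.6% | 0.20, 73.3% | 0.056, 99.8% |

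If these controls carried only half the excess risk, f = 20% would give an observed odds ratio of 1.75 and power of 68.3% (true odds ratio 1.9).

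**Effect of the planned stratification.** Suppose 40% of the 250 controls (100 women) have a breast cancer history, and an overall f of 10% (25 women) arises only from cancer treatment. All 25 then sit in that stratum, where f is 25/100 = 25%; in the other stratum it is 0. Benign surgery and natural menopause at 40 to 50 remain in both strata.

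**The case against.** **The comparator fits the stated aim.** Study Aim asks for the long-term effects of RRSO, and a contrast by RRSO status answers that. This stands: the conflict is with the hypothesis and the Discussion, not with the aim, and it does not make the main contrast wrong.

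**The power figures do not assume a clean reference group.** A reader might infer that the stated 80% and 90% rest on controls free of early menopause. The documents do not support this. The 10% calcium rate is described only by age (55 to 65), and the cognition study's controls were women without oophorectomy, not women with normal menopause. Only the bone density figure is tied to normal menopause, and its power is the least affected. The odds ratio of 1.9 and the effect size of 0.25 are detectable effects, not predictions.

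**Bias toward the null is not certain for every outcome and route.** The Discussion cites a study in which treatment-induced ovarian insufficiency did not affect cardiovascular risk, so dilution of the calcium contrast by that route is uncertain. That study does not settle bone density, cognition or the benign-surgery route.

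**The treatment route is partly handled.** Separate analyses by breast cancer history largely remove it in women without breast cancer, and treatment data are collected from medical records. In women with breast cancer it remains. Adjustment for reproductive factors might include menopausal history, but the text does not say so, and adjustment does not reclassify an exposed control.

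**Figure 2 and the full protocol are not shown.** Either could add a menopausal criterion. The eligibility text contains none, and the three passages disagree as they stand.

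**Conclusion.** The contradiction is explicit: the hypothesis and the Discussion name a reference population that the entry rule does not enforce. Benign bilateral oophorectomy and treatment-induced early menopause can put exposed women among the unexposed, which may bias the contrasts toward the null. No stated analysis uses age at or cause of menopause to detect this.

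The size cannot be determined from the document. The figures above are a sensitivity range. They assume that the hypothesis is true, that f is 10% to 20%, and that these controls carry the full early-RRSO risk. Of the three calculations, calcium at an odds ratio of 1.9 is the most sensitive, cognition less so, and bone density power hardly moves, although its estimate would shrink.

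Two stronger readings should be resisted. Women with natural menopause at 40 to 50 fall outside the hypothesis, but the document gives no ground for calling them exposed. Nor does it follow that the main reference group must be rebuilt around ovarian function at 45: that would filter one arm by natural and treatment-induced menopause with no matching filter on early-RRSO women, and could unbalance cancer treatment between the groups.

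**What to change.** 1. In Recruitment, state that women with bilateral oophorectomy for any indication before 45 are not counted as unexposed. Keep those already enrolled and analyse them separately.
2. Record age at and cause of menopause for every comparator from the study questionnaire, HEBON data and PALGA. The PALGA linkage is described for prophylactic surgery since 1991, so earlier or non-preventive operations may need the questionnaire.
3. Keep the RRSO-status contrast, which matches Study Aim, as the main analysis.
4. Prespecify a sensitivity analysis restricted to comparators with natural menopause after 50, which is the contrast in the hypothesis, and report it within breast cancer strata.
5. Reword the hypothesis and the Discussion sentence so that they describe the population enrolled.

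The cost is one derived variable and a smaller reference group in the sensitivity analysis. For scale, if 50 of the 250 comparators were dropped and there were no dilution to remove, calcium power at an odds ratio of 1.9 would go from about 79% to 71%, and cognition power from about 90% to 85%. With 136 of the 250 comparators enrolled at the last count in Results, the change can still be made while recruitment continues. It should be settled before outcomes are analysed.
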